## Methods

### BEAR intervention

BEAR (Blended E-health for children at eArly Risk) is a short and easily accessible, parent adopted and blended e-health intervention. It can be offered to parents and children aged between 12–30 months when first concerns of ASD have been expressed. The intervention is to be delivered by a trained professional working in preventive care, preferably under supervision of a professional working in specialized mental healthcare and considered to be an ASD expert, in order to obtain the best of both worlds (easy access through preventive care and expert knowledge through specialized care) and promote collaboration between different healthcare settings. The BEAR intervention consists of seven home visits and five additional e-learning sessions for parents. The first session is a general introduction module, containing psycho-education for parents about child development on the areas of play, social communication, flexible behavior and sensory interest. Next, BEAR offers five possible intervention modules aimed aforementioned areas, partially based on the DIR/Floortime model [24]. Modules include (1) improving attention to the (play) environment, (2) becoming interested in social contact, (3) increasing social contact and communication, (4) improving social communication and (5) increasing flexible behavior. At its core, BEAR is about following the child's interests, matching the child's developmental level and pace, and ensuring fun in the interaction as the basis for all further learning. A paper version of BEAR is available for parents who prefer it. An outline of the BEAR intervention’s content and planning is provided in Table 1.

**Table 1 Tab1:** Outline of the content of the BEAR intervention

Home visit	Content	Attendees	Duration
1	A twelve minute play interaction between parent and child will be videotaped, enabling professionals to generally estimate the social and communicative competencies of the child. Together with parents, three specific modules are chosen	Child, parent, BEAR professional ^a^	90 min
2–6	Parents complete e-learning modules accompanied by weekly home visits by the BEAR professional. The e-learning provides a theoretical introduction to the themes that will be discussed, are tailor made to the needs of parent and child and are implemented into practice during the home-visits	Child, parent and BEAR professional	E-learning modules take about 45 min each Home visits take about 60 min

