**Secondary outcome**				
Change in ASD symptoms	T1, T2, T3	BOSCC (parent)	RA ^b^	Yes
	T1, T3	BOSCC (clinician)	RA^c^	Yes
	T1, T3	ADOS-2	Clinician	Yes
Expressive language	T1, T2, T3	JERI	RA ^b^	Yes
	T1, T3	N-CDI	Parent(s)	
Adaptive functioning	T1, T3	Vineland Screener	Parent(s)	
Parental well-being	T1, T2, T3	WEMWBS	Parent(s)	
	T1, T2, T3	PSQ	Parent(s)	
Parental skills	T1,T2, T3	JERI	RA ^b^	Yes
`Satisfaction	T2	BESTE-O	Parent(s)	
	T2	BESTE-H	BEAR professional	
	T3	Satisfaction survey	Parent(s)	
Cost measurements	T1, T2, T3	Tic-P	Parent(s)	

*Bayley-III* Bayley Scales of Infant and Toddler Development, *BITSEA* Brief Infant–Toddler Social & Emotional Assessment-Revised, *SOV* Dutch version of the Autism Quotient (AQ), *JERI* Joint Engagement Rating Inventory, *BOSCC* Brief Observation of Social Communication Change, *ADOS-2* Autism Diagnostic Observation Schedule, *N-CDI* Dutch version of the MacArthur Communicative Development Inventory, *Vineland Screener* adapted version of the Vineland Adaptive Behaviour Scales, *WEMWBS* Warwick-Edinburgh Mental Well-being Scale, *PSQ* Parenting Stress Questionnaire (PSQ, in Dutch Opvoedingsbelastingsvragenlijst)*, BESTE* the Rating Scale Satisfaction and Effect questionnaire, *Tic-P* Trimbos and iMTA questionnaire on Costs associated with Psychiatric illness

^a^T1 is baseline; T2 is endpoint, eight weeks after baseline; T3 is follow-up, 24 weeks after endpoint

^b^Both the JERI and the BOSCC(parent) are assessed by the BEAR professional as part of the intervention (only at T1 and T2). At T3, both measurements are assessed by a researcher of the SCOPE project. All data will be coded by research assistants who are unaware of treatment allocation

^c^The BOSCC(clinician) is assessed by a professional examiner. Data will be coded by research assistants who are unaware of treatment allocation

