##### Study phase

Step 1: Baseline assessments (T1)After informed consent, parents will be asked to complete the baseline questionnaires send to them online (see Table 2). In addition, a home visit will be planned in order to film the parent–child interaction, perform semi-structured observations of the child, and testing of cognitive abilities (see Table 2).Step 2: InterventionWithin two weeks after baseline assessments, children and parents allocated to the BEAR intervention group will start with the intervention. The care-as-usual group receives either no intervention or care that is normally organized in specific cases (see Interventions section below).Step 3: End point assessments (T2)About eight to ten weeks after baseline, endpoint measures will be conducted. Parents will be asked to complete questionnaires online (see Table 2). Additionally, parents in the BEAR condition will be asked to complete an extra questionnaire to receive feedback on several aspects of the new parent training. Semi-structured observations of the child and parent–child interaction will be repeated.Step 4: Follow-up assessments (T3)Follow-up measures will take place 6 months after endpoint (see Table 2). For the last time, parents will be requested to complete online questionnaires and semi-structured observations of the child and parent–child interaction will be conducted.

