#### Data collection and management

Data collection follows the European General Data Protection Regulation. After inclusion, participants will receive an unique code number in order to anonymize all data. Non-anonymous data, for example informed consent forms, are locked in a closed cabinet and saved in protected folders, only accessible by appointed members of the research team. In order to collect and store data from the questionnaires, Castor Electronic Data Capture (Castor EDC, 2021) and QuestManager (version 5.6) software are used. Video-data will be anonymously saved on an external hard disk, which is password protected and saved in a locker.

Parents of participants are asked to complete a number of online questionnaires (see Table 2) through the QuestManager software. Parents are only able to continue to a next questionnaire if all items are answered. To prevent missing data, a researcher will call parents as a reminder and offer support if parents encountered any problems, if they fail to complete the measurements on time. Parents may withdraw from the study at any time for any reason. If this happens, researchers will try to make a final appointment with parents in order to collect the primary outcome.

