#### Statistical analysis

Data will be analyzed and reported in accordance with CONSORT guidelines. Baseline demographics (IQ, gender, age) and clinical characteristics (severity of symptoms as measured by the CoSoS) of the BEAR and CAU groups will be compared by chi-squared tests to check whether cluster randomization has led to two even groups. For the cluster RCT, all primary analyses will be intention to treat (ITT) using (generalized) linear mixed effects model for repeated measures with a random effect for cluster. Correlation of measurements (T1, T2, T3) within subject will primarily be modelled by a random effect of subject nested within clusters unless this results in insufficient fit, in which case other covariance structures will be investigated. Fixed effect in the model for baseline covariates, time and interaction with treatment condition will be included. For cost effectiveness analysis, all cost data will be accumulated. Cost differences between the two conditions will be compared. Incremental cost-effectiveness ratios will be calculated by dividing the difference in total costs by the difference in the WEMWBS.

Data collection started just before the COVID-19 pandemic. During a lockdown period where home visits were not possible because of COVID-19 restrictions, small changes were made in collecting the data and providing the BEAR intervention. Due to this, a sensitivity analysis will be undertaken, excluding participants included during the first lockdown.

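### The COVID-19 sensitivity analysis excludes by date of entry, although the problem it addresses depends on when sessions and assessments took place

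*Protocol article*

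**What the plan says.** The rule and its reason stand together in the protocol article under Statistical analysis. The background is that "Data collection started just before the COVID-19 pandemic". The trigger was a spell of lockdown in which staff could not visit families at home. In that spell, the article reports, "small changes were made in collecting the data and providing the BEAR intervention". For that reason, "a sensitivity analysis will be undertaken, excluding participants included during the first lockdown". No other COVID-19 rule appears in the article.

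The article uses inclusion to mean entry into the trial. Under Data collection and management, "After inclusion, participants will receive an unique code number in order to anonymize all data". The Abstract and the Discussion speak of inclusion of the 88 participants being complete in spring 2023, and the Discussion has follow-up data finishing later, by the end of 2023.

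After entry, each family has a series of dated contacts. A T1 home visit comes first, and families in the BEAR arm start the intervention within two weeks of it (Study phase). "The BEAR intervention consists of seven home visits and five additional e-learning sessions for parents". For T2, "About eight to ten weeks after baseline, endpoint measures will be conducted". The footnote to Table 2 gives "T1 is baseline; T2 is endpoint, eight weeks after baseline; T3 is follow-up, 24 weeks after endpoint".

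**The concern.** The altered procedures affected whoever had a session or an assessment in that period. They did not affect only those who entered the trial then. Excluding by entry date therefore goes wrong in two ways:

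- **Affected data kept.** Families who entered shortly before the period may have had BEAR sessions or T2 inside it, and they stay in. T2 matters most here, because the sample size rests on total joint engagement at the end of treatment (Sample size and power).
- **Unaffected data lost.** Families who entered during the period are removed entirely, including assessments made after home visits resumed. With 88 children in the trial, that loss also makes the check less precise.

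Arm balance is also at stake. Altered delivery can affect only BEAR families. In addition, a footnote to Table 2 says that the BEAR professional carries out the JERI and parent BOSCC assessments at T1 and T2 as part of the intervention. Altered data that remain in the set could therefore differ between arms, which is what the check should bring to light. A statement that the result is robust to the lockdown could be made with altered data still in the analysis.

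**Working it through.** The article states no figure on this point, so there is nothing to reproduce. The check is whether the scheduled contacts can overlap a lockdown.

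**Inputs from the article (weeks after T1)**
- BEAR start: 0 to 2 (Study phase).
- BEAR visits: seven, with visits 2 to 6 weekly (Table 1). If all are weekly, the last comes 6 weeks after the first, so visits span 0 to 8.
- T2: 8 to 10 (Study phase; Table 2 footnote says 8).
- T3: 24 weeks (Table 2 footnote) or 6 months, about 26 weeks (Study phase), after T2. That gives 8 + 24 = 32 to 10 + 26 = 36.

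**Assumptions, not in the article**
- Lockdown length L of 4, 8, 12 or 16 weeks.
- T1 stands in for the date of entry. The gap between consent and T1 is not given.

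**Families enrolled before the lockdown, whom the rule keeps.** Let T1 be w weeks before the lockdown starts. A contact falling a to b weeks after T1 can lie inside the lockdown if max(0, a − L) ≤ w ≤ b.

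| Contact | a to b | L = 4 | L = 8 | L = 12 | L = 16 |
|---|---|---|---|---|---|
| BEAR visits | 0 to 8 | 0–8 | 0–8 | 0–8 | 0–8 |
| T2 | 8 to 10 | 4–10 | 0–10 | 0–10 | 0–10 |
| T3 | 32 to 36 | 28–36 | 24–36 | 20–36 | 16–36 |

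Entries are weeks of enrolment before the lockdown. BEAR visits and T2 are exposed for families enrolled in the last 8 to 10 weeks before it. T3 is exposed only for families enrolled at least 16 to 28 weeks before it.

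**Families enrolled during the lockdown, whom the rule removes.** Spread entry evenly over 0 to L and put T2 at 9 weeks and T3 at 9 + 24 = 33 weeks.
- Share with T2 after the lockdown = min(1, 9/L): 100% for L = 4 or 8, 9/12 = 75% for L = 12, and 9/16 = 56% for L = 16.
- Share with T3 after the lockdown: 100% for every L considered, since 33 > 16.

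**Illustration of absolute size.** If 88 families entered evenly over an assumed 2 to 4 years (104 to 208 weeks), the 10 weeks before the lockdown would hold 88 × 10/104 = 8.5 down to 88 × 10/208 = 4.2 families. If recruitment had been open for less than 10 weeks when the lockdown began, there would be fewer.

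**The case against.** The strongest reply is that little depends on this. The article calls the changes small, the analysis is only a sensitivity analysis, and the primary analysis keeps everyone as randomised. Parent questionnaires are completed online, so mainly the videos, observations and BEAR delivery were exposed. The rule does remove families whose T1 and early BEAR visits fell in the period. Entry date also applies equally to both arms, whereas dropping only families with an altered BEAR course would remove families from one arm on the basis of what happened after allocation. Finally, the sentence is a condensed one, and a fuller plan may define the set more closely.

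Much of this stands. It limits the importance of the point and rules out a BEAR-only exclusion as the remedy. It does not remove the mismatch, because the article states both the reason and the rule, and the rule misses the reason. If the sponsor means families under treatment or follow-up during the lockdown, the wording needs correcting, since inclusion means entry elsewhere in the article.

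A reader might infer three stronger things that the article does not support:

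- **T3 is as exposed as T2.** T3 inside the first lockdown needs enrolment some 16 to 36 weeks earlier, which fits poorly with a start just before the pandemic.
- **Altered visits in later lockdowns remain in the set.** Naming a first lockdown hints at others, but the article describes altered procedures in one period only.
- **The rule misses about half of the affected families.** That would need steady enrolment for 10 full weeks before a 10-week lockdown, and neither is documented. A shorter lead-in means fewer missed families.

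**Conclusion.** The point holds for BEAR sessions and T2 of families enrolled up to about 8 to 10 weeks before the period without home visits, and for the later data of families enrolled during it. The first group can carry altered data and is kept. The second group loses T3 in every scenario considered, and T2 in 56% to 100% of cases, although those assessments came after the period.

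The number of families is unknown and may be small. The article gives no lockdown dates or enrolment counts and does not show that any family was already under treatment when restrictions began. The percentages rest on assumed lockdown lengths of 4 to 16 weeks and even entry. It would go too far to call the check worthless: it removes some of the affected data, but its set does not match the question it was added to answer. The primary intention-to-treat analysis is unaffected. This is a worthwhile correction to a supporting analysis and does not threaten the trial's main result.

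**What to change.** Define the sensitivity set by exposure, with the same rule in both arms:

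- **Version (a).** Exclude each T1, T2 or T3 assessment that fell in any period when home visits were not possible, or was done in altered form because of it. Keep the family's other assessments. The planned mixed model for repeated measures can use families with incomplete series.
- **Version (b).** Exclude families in both arms whose T1-to-T2 window overlaps such a period. This covers altered BEAR delivery without removing families from one arm only.

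State the calendar dates of the period or periods, and report by arm how many assessments and families each version removes. Wording that covers any such period does no harm if there was only one.

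The cost is a revised sentence in the analysis plan, a flag derived from assessment dates, and one additional model run. The article does not say whether the form of each contact was recorded. If it was not, the dates alone are enough for the calendar part of (a) and for (b).

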#### Data monitoring

Adverse events (AE’s) reported by the parent/primary caregiver of the participant or observed by the research team or BEAR professional will be recorded. If a serious AE occurs, the researchers will report to the ethics committee within fifteen days of first knowledge of the AE. All AEs will be followed until they have abated, or until a stable situation has been reached. As adverse events resulting from study participation are very unlikely, review or advice of a Data Safety Monitoring Board or a safety committee is not required for the current study. In accordance with the European General Data Protection Regulation, an independent data protection officer is appointed, and monitors the privacy of the participants. The research team (MS and IO) are responsible for processing the data.

## Discussion

The goal of the current study was to describe an innovative early intervention called BEAR and present the finalized study design and methods of the SCOPE study after pilot testing for feasibility. Via a cluster randomized controlled trial with two arms, SCOPE aims to compare the short term and relatively long term effects of BEAR. It is hypothesized that BEAR will lead to improved joint engagement in the parent–child interaction, decreased ASD symptoms, improved parental skills, improved satisfaction of parents with healthcare, a sooner start between first concerns and start of intervention and cost efficiency, both on short and long term (at six months). It is estimated that inclusion for the trial (*N* = 88) is completed in spring 2023 and that follow-up data are completed by the end of 2023.

Please note that the observations from the JERI and BOSCC(parent) are based on the parent–child interaction and that the parents are not an experimental fixed factor since they have been part of the intervention. However, this is not only a limitation but provides also opportunities. For it would allow to disentangle the respective contributions of the parent and the child to any change in the parent–child interaction and the child’s social-communicative behaviour. Furthermore, in addition to the JERI and BOSCC(parent) we will observe the child’s behaviour in the ADOS procedure and a separate BOSCC(clinician) procedure. Here, the child is interacting with a professional examiner who has not been part of the intervention. The analysis of the ADOS and BOSCC(clinician) data is an important back-up to the analysis of the JERI and BOSCC(parent) data by creating the possibility to compare the child’s behaviour while interacting with the parent and with another adult. Furthermore, for our experimental group, there might be bias at our T1 and T2 video measurements, due to the interventionist being the assessor of the JERI and BOSCC. Since data are coded by skilled observers who are not part of the intervention and are unaware of treatment allocation, we hope to minimize this possible bias. This will further be discussed within our finalized paper reporting results of the SCOPE study.

So far, several studies examined the importance and effectiveness of early identification and early intervention programs in high-risk groups. However, still several barriers exist as why very young children at high likelihood of ASD receive adequate care later then preferred. The ongoing SCOPE study in which the BEAR intervention plays a pivotal role can help to overcome these barriers. It is specifically designed as a non-stigmatizing answer to difficulties in those children that are at risk at being identified too late due to a less specific phenotype. Also, when difficulties in parent-professional conversations exist regarding developmental concerns, BEAR might be a solution in offering adequate early care.

## Data Availability

The final dataset of the randomized controlled trial will be available (anonymized) for other researchers at the end of the study.

## Abbreviations

ADOS-2: Autism Diagnostic Observation Schedule
AE: Adverse Event
ASD: Autism spectrum disorder
Bayley-III: Bayley Scales of Infant and Toddler Development
BEAR: Blended E-health for children at eArly Risk
BESTE: The Rating Scale Satisfaction and Effect questionnaire
BITSEA: Brief Infant–Toddler Social & Emotional Assessment-Revised
BOSCC: Brief Observation of Social Communication Change
CoSoS: Communication and Social development Signals
JERI: Joint Engagement Rating Inventory
N-CDI: Dutch version of the MacArthur Communicative Development Inventory
PSQ: Parenting Stress Questionnaire (PSQ, in Dutch Opvoedingsbelastingsvragenlijst)
RCT: Randomized controlled trial
SCOPE: Social COmmunication Program supported by E-health
SOV: Dutch version of the Autism Quotient
Vineland Screener: Adapted version of the Vineland Adaptive Behaviour Scales
WEMWBS: Warwick-Edinburgh Mental Well-being Scale
Tic-P: Trimbos and iMTA questionnaire on Costs associated with Psychiatric illness
